#### Mechanistic outcomes

The degree and anastomotic locality of different immune cell populations, especially CD8+ T cells, will be compared before and after each intervention utilising high‐parameter flow cytometry (Appendix 3). This will be studied using matched mucosal samples taken at the time of surgery and at endoscopic follow‐up, in a minimum of 140 participants.

### Participant timeline

A study flowchart (Figure 1) and the assessments schedule (Table 1) demonstrate the participant journey through the study.

**FIGURE 1 codi70212-fig-0001:**
[figure not shown]
Study flowchart demonstrating participant journey through the trial from identification, enrolment, treatment allocation and follow‐up.

**TABLE 1 codi70212-tbl-0001:** Schedule of assessments during the study.

	Baseline	Operation	6 weeks	12 months (−6 to +3 months)	Study end (up to 5 years)
Eligibility assessment	X	X			
Consent	X				
Medical history	X				
Concomitant medications	X		X	X	X
Demographics	X				
IBD‐Control	X		X	X	
CDAI	X		X	X	
EQ‐5D	X		X	X	
Randomisation		X			
Mesenteric disease activity index		X			
Adverse events		X	X	X	
Colonoscopy				X	X (via note review)
Blood samples	X			X	
Mucosal/mesenteric biopsies		X		X	
Surgical recurrence				X	X (via note review)

### Sample size

The primary outcome will be the time to endoscopic recurrence (ER) post‐randomisation (Modified Rutgeerts score ≥ i2). All participants will be followed up for a minimum of 6 months post‐randomisation and up to a maximum of 3 years. The best existing data indicates ER rates of approximately 65% on conventional surgery and 24% on Kono‐S surgery at 12 months [34]. Other published data on the rate of endoscopic recurrence after conventional surgery varies from 58% to 93% [28, 35, 36, 37]. The systematic review unfortunately found no published data on the ER rates after close or extended mesenteric resection [16]. In a survey of 34 surgeons, 71% were persuaded to change practice based on a reduction in endoscopic recurrence to 30% or less after 12 months.

The sample size calculation for the 2 × 2 factorial design assumes: 90% power; 5% (two‐sided) significance level; and estimated reduction in 1‐year endoscopic recurrence rates from 52.5% to 32.5%. Using the Freedman method a total of 112 recurrences are required [38]. After accounting for surgeon effects (assuming each of 12 sites would have 2 surgeons, an ICC of 0.01 and 15 patients per surgeon) and an attrition rate of 3%, the target sample size is 154 per group for each comparison.

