#### Standard of care

Standard care is essentially surgeons' preference of anastomosis. Anastomosis may utilise staples or sutures and has a configuration of either end to end, functional end to end, or end to side.

The mode of access (open/laparoscopic/robotic), closure technique and post‐operative care are according to usual practice for that participating centre.

For all groups the mesenteric incision will be made proximal to the mesenteric transition zone [27], while the distal incision will be placed where both the mesentery and intestine are macroscopically normal immediately distal to the region of disease. Each technique consists of components familiar to bowel surgeons.

Every participating surgeon will have been mentored for the Kono‐S anastomosis and will have carried out at least 2 procedures outside the trial. A video of each technique will be created and distributed to all surgeons. We will run dedicated training sessions for all surgeons involved in the trial. Two independent reviewers will review images of the resection specimen to ensure adequate quality and extent of mesenteric excision.

Post‐operative follow‐up and colonoscopic assessment at 6–12 months are part of standard practice [28]. Localisation of recurrence will be aided by a tattoo of the mesenteric border of the anastomosis at the time of surgery using carbon black.

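### The guaranteed follow-up of 6 months is shorter than the 12-month basis of the sample size, ends as the only scheduled colonoscopy window opens, and contradicts the Data collection section, so 90% power is not assured

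*Protocol article*

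**What the plan says.** The Sample size section sets the follow-up: "All participants will be followed up for a minimum of 6 months post‐randomisation and up to a maximum of 3 years". The same section powers the trial on an "estimated reduction in 1‐year endoscopic recurrence rates from 52.5% to 32.5" per cent, with 90% power and a "5% (two‐sided) significance level". It continues: "Using the Freedman method a total of 112 recurrences are required". It then inflates for surgeon effects, "assuming each of 12 sites would have 2 surgeons, an ICC of 0.01 and 15 patients per surgeon", and for 3% attrition, and arrives at 154 per group for each comparison, 308 in all.

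Other sections describe follow-up and colonoscopy timing differently:

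- **Table 1** has one scheduled colonoscopy, in the column headed "12 months (−6 to +3 months", that is, months 6 to 15. A later colonoscopy is picked up only by note review at study end.
- **Standard of care** says that follow-up and "colonoscopic assessment at 6–12 months are part of standard practice". The Discussion also gives 6 to 12 months.
- **Introduction** describes a 1-year follow-up, minus 6 or plus 3 months.
- **Data collection** places the end-of-study data between 12 and 57 months after surgery. With up to 45 months of recruitment, 57 = 45 + 12, so the last recruit reaches 12 months.
- **Primary outcome** and **Statistical methods** run the time to recurrence up to 3 years.

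**The concern.** The primary outcome is a modified Rutgeerts score, so a recurrence is observed only if a colonoscopy is done. A patient with exactly the guaranteed 6 months can complete follow-up on the day the window opens, with no primary-outcome assessment. The conversion of 112 recurrences into 308 patients, by contrast, credits every patient with a 12-month recurrence probability.

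At stake is the number of observed recurrences behind both factorial comparisons. Late recruits lost because data collection closes too early would come on top of the 3% attrition. The best- and worst-case imputation in Statistical methods is a sensitivity analysis and does not restore the lost events.

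**Working it through.** **1. The plan's own figure.** Under constant hazards, HR = ln(0.675)/ln(0.475) = 0.528. Freedman: events = [(1 + 0.528)/(1 − 0.528)]² × (1.960 + 1.282)² ≈ 110.1, rounded up to 111, against 112 stated. The mean 1-year rate is (0.525 + 0.325)/2 = 0.425. The design effect is 1 + (15 − 1) × 0.01 = 1.14. Then 112/0.425 × 1.14/0.97 = 309.7 (306.9 from 111 events), against 308. The figure reproduces, and only with 12 months of observation for everyone.

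**2. Assumptions for the check** (not fixed by the article): constant hazards from the stated 1-year rates, uniform accrual over 45 months, one colonoscopy per patient, and no later colonoscopy counted.

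**3. Patients not yet scoped.** If data close L months after the last randomisation and colonoscopy is at month t, the unscoped share is the mean of max(t − L, 0), divided by 45.

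- L = 6, t even over months 6–12: 3/45 = 6.7%, 308 × 0.067 ≈ 20.5 patients.
- L = 6, t even over months 6–15: 4.5/45 = 10%, about 31 patients.
- L = 6, t = 12 for all: 6/45 = 13.3%, about 41 patients.
- L = 12, t even over months 6–15: (3/9 × 1.5)/45 = 1.1%, about 3 patients.
- L = 12, t no later than 12: none.

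**4. Recurrences and power.** The recurrence probability at month t, averaged over the two levels of a factor, is 0.5[(1 − 0.475^(t/12)) + (1 − 0.675^(t/12))]. With p its mean over scoped and unscoped patients (zero for the unscoped), events E = 308 × 0.97 × p. Power = Φ(√(E/1.14) × 0.309 − 1.96), where 0.309 = (1 − 0.528)/(1 + 0.528). The last column omits the 1.14.

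| Data close after last randomisation | Colonoscopy timing | Recurrences | Power with 1.14 | Power without |
|---|---|---|---|---|
| 6 months | months 6–12 | 94 | 80% | 85% |
| 6 months | months 6–15 | 101 | 83% | 87% |
| 6 months | all at 12 | 110 | 86% | 90% |
| 12 months | months 6–12 | 101 | 83% | 87% |
| 12 months | months 6–15 | 112 | 86.5% | 90.5% |
| 12 months | all at 12 | 127 | 90.3% | 93.6% |
| 15 months | months 6–15 | 114 | 86.9% | 90.9% |

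**5. What later colonoscopies would add.** Suppose a random share of patients without a recorded recurrence has a further colonoscopy in months 24–36 where the calendar allows. With a 6-month close and first colonoscopies in months 6–15, a share of 20% gives 86.1% and 50% gives 89.9%. With a 12-month close, about 20% (first colonoscopies in months 6–15) or 30% (months 6–12) brings power to within a point of 90%.

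**The case against.** The strongest reply is that no 6-month data close is stated anywhere. The Data collection section implies 12 months for the last recruit. On that timeline about 1% of patients are unscoped, and extending to 15 months gains only 0.4 points (86.9% against 86.5%). This stands: what remains below 90% then comes from colonoscopies done before month 12, and the even spread over the window is an assumption, since Table 1 labels the visit 12 months. With colonoscopies over months 9–15 and the 12-month close, power is 89.7%.

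A second reply is that the outcome runs to 3 years. If recurrences up to 3 years count as detected when they occur, power is about 98%, and about 97% even if everyone with under 12 months contributes nothing. Counting to 12 months only, with the 6-month minimum, gives 89.5%. These figures are upper bounds, because they treat recurrence as detected continuously, whereas after month 15 the article offers only note review. Counting no later colonoscopy is the opposite extreme, so the truth lies between.

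A reader might infer two stronger things. One is that 308 patients fail to deliver 90% power. The documents do not support this: the calculation reproduces, and the shortfall depends on the closing date, colonoscopy timing and later detection. The other is that 128 recurrences (112 × 1.14) are needed where the plan allows 112. That inflation is already inside the 308, since 308 × 0.97 × 0.425 = 127.

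**Conclusion.** The concern holds as an inconsistency with a measurable consequence. The guaranteed follow-up is shorter than the horizon used for the sample size, ends as the colonoscopy window opens, and contradicts the Data collection section.

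Applied literally, it could leave 7% to 13% of patients without a primary-outcome assessment, more than twice the 3% allowed, with power of about 80% to 86%. On the 12-month reading, loss from the closing date is negligible and power is about 83% to 90%, or higher with later recurrences from the notes. All these figures include the plan's surgeon inflation and count no later colonoscopy; they also rest on constant hazards and uniform accrual. The stated 90% is therefore conditional on follow-up and colonoscopy timing that the article does not settle. It is worth correcting while the wording can still be changed.

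**What to change.** 1. Reconcile the follow-up and colonoscopy timings in the Introduction, Standard of care, Table 1, Sample size, Data collection and Discussion.
2. In Sample size, replace the 6-month minimum with follow-up of the last patient to the close of the colonoscopy window, and say that the primary analysis will not be run before that date.
3. Beside the 112 and 308, give the expected number of recurrences and the power at the planned colonoscopy times. Give a range with its assumptions on accrual, colonoscopy timing and later colonoscopies found by note review, not one restated figure.

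The cost is wording, a power statement that may be slightly less favourable, and at most 3 months more for the last patients than Data collection implies (none if the reconciled window closes at 12 months). It needs no extra patients or procedures.

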### Recruitment

Potential participants will be discussed at MDT meetings and identified at the time of pre‐operative assessment before the day of surgery. Potential participants will be approached either at their clinic visit prior to surgery or pre‐operative assessment. The study will be run nationally within the United Kingdom across up to 27 centres, recruiting one participant per month over a maximum of 45 months.

### Allocation

Once consent has been obtained (Appendix 1), baseline data recorded and eligibility confirmed, participants will be centrally randomised using the CTRU online randomisation system (SCRAM). Randomisation will occur intraoperatively when all eligibility criteria are met. The doctor or research nurse will access the web‐based randomisation system, enter patient demographic details (ID, date of birth) and the treatment allocation will be returned.

Participants will be allocated using a computer‐generated pseudo‐random list, stratified by centre, with random permuted blocks of varying sizes. The sequence will be restricted by authorisation until analyses are complete.

### Blinding

As there is no difference between the interventions in abdominal access or closure, it is easy to blind the participant. Those assessing the 12‐month endoscopic outcomes will be blinded to the allocation. Endoscopists may recognise the Kono‐S anastomosis in the bowel configuration but will not be directly involved in the study. The degree of mesenteric excision will not be apparent during colonoscopy.

### Data collection

Baseline data will be collected by a research nurse or clinician using specific case report forms (Table 1). Participants will be given a diary to complete 7 days prior to the day of surgery to enable the Crohn's Disease Activity Index (CDAI) to be calculated (Appendix 2). Operative details will be recorded by the operating surgeon. Six‐week and 6‐ to 12‐month follow‐up data will be collected by a research team member who is blind to allocation. Standard colonoscopic follow‐up will be collected by a colonoscopist not involved in the trial. Colonoscopists will collect mucosal biopsies and recurrence data, relative to the small bowel mesenteric tattoo. At the end of the study (12–57 months after surgery) further data will be collected by a team member who is blind to allocation.

Participants may withdraw their consent for the study at any time. Although the participant is not required to give a reason for discontinuing their study treatment, a reasonable effort will be made to establish this reason while fully respecting the participants’ rights.

### Data management

Participant confidentiality will be respected, and the principles of the UK Data Protection Act (DPA) followed. The investigator will ensure that identifiable data is kept securely.

All participants will be assigned a unique study ID number at screening that will link the clinical information collected for them on the study database. All CRFs will only identify the participant by their study ID number.

Study records, including source data, will be stored for 10 years after the completion of the study by participating sites, before being destroyed. Access will be restricted to authorised individuals.

Data management will be provided by the University of Sheffield Clinical Trials Research Unit (CTRU) and a separate data management plan (DMP) will detail activities for the study in accordance with local SOPs.

### Statistical methods

The primary outcome is the time to endoscopic recurrence (ER), over a follow‐up of up to 3 years, defined as a Modified Rutgeerts score [≥i2]. Patients without a reported ER will be censored at their last known date of not having had ER. The primary effectiveness analysis, on the intention‐to‐treat (ITT) sample, will compare the time to ER, between the two factors (Kono‐S vs. standard anastomosis surgery; extended mesenteric resection vs. close mesenteric resection) using a mixed‐effects parametric survival model with random effects for centre and surgeon and fixed effects for the two factors. The model will be implemented using a Weibull survival distribution.

It is anticipated that there will be no interaction between the two factors. To test this assumption, the initial statistical model will include an interaction (Kono‐S (yes or no) vs. extended mesenteric resection (yes or no)) term between the two factors. We will report the estimate of the interaction term and its associated 95% confidence interval (CI).

If the CI for the hazard ratios (HR) for the interaction term shows no evidence of an interaction, then we will analyse the data, without the interaction term, using the simpler factorial design with the two main factors. The CIs for the HRs for the Kono‐S versus standard anastomosis contrast and extended mesenteric resection versus close resection contrasts will be reported from this simpler model. If the CI for the HR for the interaction term demonstrates evidence of an interaction, then we will analyse the data using the four randomised groups separately, with standard anastomosis and close mesenteric resection as the reference treatment. The treatment effects and corresponding 95% CIs will be presented for all relevant comparisons.

We will complement the ITT analysis of the primary outcome with several sensitivity analyses. A per protocol analysis will estimate the efficacy of the Kono‐S versus standard anastomosis and extended versus close mesenteric resection in participants who adhere to the main aspects of the protocol. For participants who do not have a colonoscopy during the trial, or whose Modified Rutgeerts score was not completed, missing data will be imputed through best‐ and worst‐case scenarios to investigate the impact of assuming informative missingness (missing not at random assumptions).

Secondary endpoints will be analysed as follows: Time‐to‐event outcomes will be analysed as per the primary outcome. Binary outcomes will be compared between the two factors ((1) Kono‐S vs. standard anastomosis and (2) extended vs. close mesenteric resection) using a multi‐level mixed effects logistic regression model with adjustment for baseline covariates, with associated ORs and 95% CIs. Absolute risk differences with 95% CIs will also be presented for binary outcomes. Continuous outcomes will be analysed using a multi‐level mixed effects regression model with adjustment for baseline covariates. All multi‐level models will use the same covariates as the primary analysis model. The serious adverse event (SAE) rates in the post‐randomisation period will be compared between the four randomised groups using a chi‐squared test and 95% CIs for each of the four randomised groups. We will also count the total number of SAEs experienced by each patient and compare counts using a Poisson generalised linear model (GLM) and reporting the risk ratio and associated 95% CIs.

Regardless of the statistical significance of the overall effect, exploratory subgroup analyses will be carried out for the primary outcome (ER). We will carry out subgroup analyses to examine if treatment effects differ based on patient demographics, disease phenotype and medical treatment history. As this trial is not formally powered for subgroup analyses, all subgroup effects will be considered exploratory, and *p*‐values will not be presented.

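### Recurrence is seen only at colonoscopy, so its time is interval-censored; the stated right-censored Weibull model makes no allowance for this, and if most patients have one colonoscopy the HR moves from 0.53 to about 0.61 and power to about 65–77%

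*Protocol article*

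**What the plan says.** The Statistical methods section of the protocol article defines the endpoint and its horizon: "The primary outcome is the time to endoscopic recurrence (ER), over a follow‐up of up to 3 years", with recurrence being a Modified Rutgeerts score of at least i2. The primary analysis is a "mixed‐effects parametric survival model with random effects for centre and surgeon and fixed effects for the two factors", and "The model will be implemented using a Weibull survival distribution". The only rule about times is the censoring rule: "Patients without a reported ER will be censored at their last known date of not having had ER". The section gives no rule for the event date and does not mention interval censoring. Its sensitivity analyses are a per-protocol analysis and best- and worst-case imputation for missing colonoscopies or scores.

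Table 1 has one colonoscopy visit, in the column "12 months (−6 to +3 months", and one study-end entry marked "X (via note review". The Standard of care section says that "colonoscopic assessment at 6–12 months are part of standard practice". Under Sample size, patients are "followed up for a minimum of 6 months post‐randomisation and up to a maximum of 3 years". That section assumes 1-year recurrence of 52.5% against 32.5%, two-sided 5% significance and 90% power. It uses the Freedman method to reach 112 recurrences and 154 per group for each comparison.

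**The concern.** A score-defined recurrence has no observable onset. With one colonoscopy, a positive result places onset anywhere between randomisation and that date, and a negative result places it later. These are interval-censored data. A Weibull model that takes the colonoscopy date as the event time fits the timing of appointments rather than of disease.

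Suppose colonoscopy timing is unrelated to recurrence. The rate of recorded first positives at time t is then the cumulative risk F(t) multiplied by the rate of colonoscopy. The ratio between arms is F₂(t)/F₁(t), a risk ratio, which lies closer to 1 than the hazard ratio behind the sample size. This concerns the primary analysis of both factors. The Freedman calculation assumes that event times are observed, so its 90% power does not carry over automatically.

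**Working it through.** **Inputs from the Sample size section.** 1-year recurrence 52.5% and 32.5%; two-sided 5%; 90% power; ICC 0.01 with 15 patients per surgeon; 3% attrition; 154 per group. Table 1 gives the colonoscopy window, months 6–15.

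**1. Reproduce the plan's figure.**
- Planned HR = ln(0.675)/ln(0.475) = 0.528.
- Freedman events = (1.960 + 1.282)² × [(1 + HR)/(1 − HR)]² = 110.1, rounded up to 111. With the HR rounded to 0.53 it is 112, as stated.
- Mean risk = (0.525 + 0.325)/2 = 0.425. Design effect = 1 + 14 × 0.01 = 1.14.
- Total = 111/0.425 × 1.14/0.97 = 307, or 308 when each step is rounded up. With 112 events it is 310–311. The stated 308 is reproduced.
- Per arm, 154 × 0.97 = 149 after attrition, and 149/1.14 = 131 after removing the design effect as well. The 131 is the like-for-like figure for a calculation without clustering.

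**2. What an exact-date analysis estimates.** With exponential times at the plan's rates, F(t) = 1 − S(12)^(t/12). The ratio F₂/F₁ is:
- month 6: 0.178/0.311 = 0.574
- month 12: 0.325/0.525 = 0.619
- month 15: 0.388/0.606 = 0.641

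**3. Power by hand, one colonoscopy at month 12, date taken as exact.** SE ≈ √(1/d₁ + 1/d₂), where d₁ and d₂ are the expected events per arm, and log(0.619) = −0.480.
- n = 131: d = 68.8 and 42.6, SE 0.195, z = 2.46, power 69%.
- n = 149: d = 78.2 and 48.4, SE 0.183, z = 2.62, power about 74–75%.

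Reaching 112 events does not protect power. With a ratio of 0.619, Freedman's formula needs 10.507 × (1.619/0.381)² ≈ 190 events.

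**4. The same colonoscopy analysed as interval-censored.** Var(log HR) = Σ p/[n(1 − p)(ln(1 − p))²] = 0.0152 + 0.0238 = 0.0390 at n = 131. SE = 0.198, z = 0.639/0.198 = 3.23, power 89.9%. At n = 154 it is 93.9%.

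**5. Simulation.** One factor, no random effects, true HR 0.528, exponential times, Weibull model with the colonoscopy date as event time, 1,500 trials per row. The last two rows rest on assumed scan patterns.

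| Observation of recurrence | n per arm | Mean HR | CI coverage of 0.528 | Power |
|---|---|---|---|---|
| Exact times to month 12 | 131 | 0.52 | 94% | 92% |
| One colonoscopy, months 6–15 | 131 | 0.61 | 90% | 67–68% |
| One colonoscopy, months 6–15 | 154 | 0.61 | 90% | 76% |
| One colonoscopy, near month 12 | 131 | 0.62 | 84–85% | 68% |
| Half have a second, 9–21 months later | 131 | 0.55 | 93% | 94% |
| About annual to 3 years | 131 | 0.53 | 95% | 99% |

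With one colonoscopy the fitted Weibull shape was about 5 to 14 against a true value of 1. True shapes of 0.7 and 1.4 gave the same HR (0.61) and power (67–68%). A separate simulation gave HR 0.60–0.62, coverage 86–92%, and power 65–70% at 131 and 73–77% at 149. An interval-censored Weibull fit to one colonoscopy in months 6–15 (400 trials, n = 131) gave HR 0.52, coverage 97% and power 87%.

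**The case against.** **The event-date rule is inferred.** The quoted rule covers only patients without recurrence. A Weibull model can be fitted to interval-censored data, and the full protocol or analysis plan, neither shown, may say so. This stands as a limit on certainty. The article does, however, state the distribution, the censoring rule and a sample size method for observed event times. Right-censoring is the only kind it describes, and no listed sensitivity analysis deals with unknown recurrence time.

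**Later colonoscopies.** Follow-up runs to 3 years and the notes are searched at study end. As the last rows of the table show, the attenuation then largely disappears. This stands, so a reader who infers that the trial has lost its 90% power goes further than the documents allow. Equally, nothing in the article schedules or counts those later examinations.

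**False positives.** A reader might infer inflated type I error. With one colonoscopy in months 6–15 the null rejection rate was 3.5%, so the coverage loss there comes from an HR centred in the wrong place. Across other visit spreads it reached about 7.5%, and with later colonoscopies it was 6–7%, a modest excess.

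**Re-operated patients.** A reader might also infer that someone re-operated without a scored colonoscopy is wrongly treated as recurrence-free. The article does not say how such patients enter the main analysis. Surgical recurrence is a separate secondary outcome, and missing scores have best- and worst-case imputation. Counting re-resection as an event would redefine the primary endpoint.

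**The remedy is not a full rescue.** With colonoscopies spread over months 6–15 and 131 per arm, interval censoring gives about 87%, slightly under 90%.

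**Conclusion.** The point holds in conditional form. Recurrence times are interval-censored by design, and the stated model and censoring rule make no provision for that. If the colonoscopy date is used as the event time and most patients have only the scheduled examination, the reported HR is about 0.61 rather than 0.53, and coverage and power fall to the levels shown in the working. If many patients have later colonoscopies, the bias is small and power exceeds 90%.

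The figures assume the plan's 1-year rates, proportional hazards, colonoscopy timing unrelated to recurrence, and no random effects. The size of the problem depends on how many patients have a later scored colonoscopy, which the article does not give. Under the one colonoscopy the trial itself schedules, the 90% claim is not supported for an exact-date analysis.

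**What to change.** Keep the mixed-effects Weibull model and state that it is fitted with the interval-censored likelihood. For a patient with recurrence, the interval runs from the last colonoscopy scored below i2 (or randomisation, if none) to the first scored i2 or worse. Other patients are right-censored at their last colonoscopy scored below i2. Keep the two factors as fixed effects and centre and surgeon as random effects.

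With one colonoscopy per patient, this is equivalent to a mixed complementary log-log regression of recurrence on the two factors, with log time from randomisation to colonoscopy as a covariate. It returns the same HR and can be fitted in standard software.

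Report the exact-date Weibull model as a sensitivity analysis. The endpoint definition stays as it is. The cost is a change of wording and slightly more programming, with no extra visits or patients.

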There are commonalities with the techniques of Kono‐S anastomosis and extended mesenteric resection that may explain their potential effectiveness. Both isolate the anastomosis from the diseased mesentery. Kono‐S achieves this through a totally antimesenteric anastomosis placed as far away as possible from the mesentery, while extended mesenteric resection removes the theoretical disease driver. A combined approach is technically feasible and may improve efficacy. If either or both interventions result in reduced recurrence, understanding the underlying mechanism of action becomes a crucial question. To explore this, we will examine the locality of any mucosal recurrence. The prevailing notion is that CD arises from the interplay of genetically inheritable traits and environmental factors, including the microbiota, leading to innate and adaptive immune cell‐mediated inflammation [22]. Analysing the immune cell phenotypes in the mucosa of the different combinations of resection and anastomosis will provide insights into the impact each intervention has on the mechanism of inflammation [23, 24, 25]. Examining visceral fat area, anastomotic locality of immune cell populations, with a specific focus on T cell activation and exhaustion, will enable us to explore potential underlying mechanisms of action.

We propose a protocol for a UK multicentre, superiority, 2 × 2 factorial, randomised, open‐label trial with a 1‐year follow‐up (−6 months/+3 months). Participants will be randomised (1:1:1:1) to one of four groups:
Kono‐S + extended mesenteric resection;Kono‐S + close mesenteric resection;Standard anastomosis + extended mesenteric resection;Standard anastomosis + close mesenteric resection.

Our trial will investigate relevant clinical and mechanistic outcomes on: (1) the Kono‐S anastomosis; (2) extended mesenteric excision; (3) the locality of recurrence after surgery; and (4) local tissue immune response and its association with surgical recurrence.

The main aim of the study is to compare recurrence after standard mesenteric excision or extended excision and standard anastomosis or Kono‐S anastomosis (with or without extended mesenteric excision).

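### A preliminary interaction test chooses between the factorial main effects and four-group contrasts as the primary result; type I error rises modestly and the fallback branch is not covered by the stated 90% power

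*Protocol article*

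**What the plan says.** In the protocol article, Statistical methods opens by naming the primary analysis: a mixed-effects Weibull model on the intention-to-treat sample, comparing the two factors, with a fixed effect for each. It then states the expectation: "It is anticipated that there will be no interaction between the two factors". To check this, an initial model includes the interaction term, whose estimate and 95% confidence interval will be reported.

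The interval then decides the next step. If it shows no evidence of interaction, the term is dropped and the two main-effect hazard ratios are reported. If it does show evidence, "then we will analyse the data using the four randomised groups separately, with standard anastomosis and close mesenteric resection as the reference treatment". The section adds that effects and intervals will be given for every relevant comparison, without listing them. It gives no criterion other than the interval.

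The Sample size section covers only the two-level comparisons: "90% power; 5% (two‐sided) significance level", a fall in one-year recurrence from 52.5% to 32.5%, and "Using the Freedman method a total of 112 recurrences are required". The target is 154 per factor level, 308 in all. It gives no power for the interaction or for single-cell contrasts.

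**The concern.** This is a test-then-choose rule. Three consequences follow.

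- When the interaction is significant by chance, the cell estimates that produced it are extreme by selection. Ordinary 5% tests and 95% intervals on those cells are then no longer calibrated.
- The fallback compares quarters of the trial rather than halves, so the design power does not carry over.
- When the interaction is not significant, the simpler model is adopted on the strength of a test with little power. The Introduction gives some reason not to take additivity for granted, since it says of the two techniques that "Both isolate the anastomosis from the diseased mesentery".

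At stake is whether the primary hazard ratios keep the error rate and power for which the trial was sized.

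**Working it through.** **Inputs** (protocol article, Sample size unless noted): two-sided 5%; 90% power; 52.5% vs 32.5%; 112 events; "an ICC of 0.01 and 15 patients per surgeon"; 3% attrition; 154 per level; 1:1:1:1 allocation (Abstract).

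**The plan's own figures**
- HR = ln(1 − 0.325)/ln(1 − 0.525) = 0.528, so |log HR| = 0.639.
- Freedman: (1.960 + 1.282)² × (1.528/0.472)² = 110.1, so 111 events against the stated 112.
- Mean risk is 0.425, so N = 112/0.425 ≈ 264. With design effect 1 + 14 × 0.01 = 1.14 and 3% attrition, 264 × 1.14/0.97 ≈ 310, against 308.

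The stated design therefore reproduces closely.

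**Events for the check.** All of 308 give 308 × 0.97 × 0.425 ≈ 127 events. Deflating for clustering, 127/1.14 ≈ 111. So 112 to 127 brackets the information available.

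**Variances** (normal approximation, D events equally spread over four cells, random effects ignored): main-effect log HR 4/D; single-cell contrast 8/D; interaction 16/D. The main-effect and interaction statistics are then independent.

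**Type I error of the rule.** A simple-effect statistic is (Z_main ± Z_int)/√2. By simulation, given |Z_int| > 1.96 and a null factor, the contrast with the reference cell is significant in 34%, and at least one of the two simple effects in 65%.
- Reference contrast only: 0.95 × 0.05 + 0.05 × 0.34 = 0.0645.
- Either simple effect: 0.95 × 0.05 + 0.05 × 0.65 = 0.080.
- Main effect fixed in advance: 0.050.

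**Overall power with no true interaction, 112 events.** The fixed main effect has statistic 0.639/√(4/112) = 3.38, giving 92.2%. After a chance trigger the reference contrast has 52%. Two-stage: 0.95 × 0.922 + 0.05 × 0.52 = 0.902.

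**Power of a cell contrast at HR 0.528.** Each cell has 308 × 0.97/4 = 74.7 patients.
- 112 events: 0.639/√(8/112) = 2.39, power 67%.
- 127 events: 0.639/√(8/127) = 2.54, power 72%.
- Unequal events, 74.7 × 0.525 = 39.2 and 74.7 × 0.325 = 24.3: SE 0.258, power 70%.
- Freedman's formula gives 64–69%.

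**Power of the interaction test for a hazard-ratio ratio of 1.89 (= 1/0.528).**
- 112 events: SE 4/√112 = 0.378; 0.639/0.378 = 1.69; power 39%.
- 127 events: SE 0.355; 0.639/0.355 = 1.80; power 44%.
- The 95% interval spans a factor of exp(1.96 × 0.355) = 2.0 to exp(1.96 × 0.378) = 2.1 either way. A ratio of about 2.7 to 2.9 is needed for 80% power.

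**If the techniques are redundant.** Assume one-year risks of 65% in the reference cell and 40% in the other three; these are not protocol figures. The true HR against the reference is ln(0.60)/ln(0.35) = 0.49. With 74.7 patients per cell, the interaction test misses the pattern in 46% of trials. The fixed main effect averages to HR about 0.67, with about 63% power; the two-stage rule has about 82%.

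**The case against.** The strongest reply is that the rule is written down, its fallback has a named reference group, and the damage is small overall. That is largely right. With no true interaction the fallback triggers in 5% of trials, about two points of power are lost, and the 90% target is still met. The 34% describes that rare branch, not the trial as a whole.

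Some stronger readings are tempting but unsupported:

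- A reader might infer that no primary contrast was fixed. The section does name the two factor comparisons as primary, and the sample size rests on them.
- A reader might infer that the trial forfeits its 90% power. Only the fallback contrasts lack it.
- A reader might take 8.0% and 65% as the main figures. They need the broad reading of which comparisons are relevant; the named reference group fits 6.5% and 34% better. On the broad reading, overall power is not lost either.
- A reader might infer that the Introduction contradicts the no-interaction expectation. It says that combining the techniques may improve efficacy, and the Abstract speaks of an additive effect. Overlap is plausible, not shown.
- A reader might infer that the interaction is ignored once non-significant. The protocol commits to reporting its estimate and interval.

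One objection bears on the remedy. Under the assumed redundancy, the switch is more powerful than the fixed main effect (82% against 63%). That stands, so the fix is a trade-off.

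**Conclusion.** The concern holds in a moderate form. A weak preliminary test chooses the primary contrast, type I error per factor rises from 5.0% to about 6.5%, and the alternative branch has about 67–72% power for the planned effect. Finding no evidence of interaction is weak support for the no-interaction model, because an interaction as large as the planned effect would be missed in 56–61% of trials. The overall power cost under the protocol's own assumption is slight (about 92% to 90% at 112 events).

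These figures rest on reading the 95% interval as a two-sided 5% test, on equal events per cell except where stated, and on ignoring the centre and surgeon random effects. The if/then rule stands in the protocol article itself, so it is not a detail merely left to an analysis plan.

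**What to change.** Keep the two main effects from the no-interaction factorial model as the primary analysis whatever the interaction shows, and delete the conditional switch. Always report the interaction hazard ratio with its 95% interval and the four-group estimates against the reference cell, labelled as pre-specified supportive results.

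Under the protocol's no-interaction assumption this restores 5.0% error per factor and the design power (90.5% by Freedman, 92.2% by Schoenfeld, at 112 events). It takes one paragraph of wording, with no change to recruitment, data collection or treatment, and should be made before outcome data are unblinded.

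The plan should state the downside: under a real interaction each primary hazard ratio averages over the levels of the other factor and can lose power, so it must be interpreted alongside the four-group table.
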